### Experimental design

This is a single-blind (outcome assessor), two-arm, randomised controlled trial (RCT). Adults with asthma will be invited to participate in the study after a regular medical visit, and asthma pharmacotherapy will be maintained during the intervention. All of the eligible participants will be randomly assigned to either a control group (CG) or an intervention group (IG). Both groups will receive usual care (pharmacological treatment) and similar educational programmes. In addition to these, participants in the IG will undergo the behaviour intervention based on feedback, which aims to increase participation in physical activity. Both before and following the completion of the intervention period, data will be collected on asthma clinical control, levels of physical activity, health-related quality of life, asthma exacerbation, levels of anxiety and depression symptoms. Anthropometric measurements will also be collected. Information on comorbidities, lung function and the use of asthma medications will be extracted from the participant’s medical records. The protocol foresees has 12 weeks including 8 weeks of intervention and 4 weeks of evaluation (2 weeks before and 2 after the intervention). The study flow diagram is presented in Fig. 1 and the study schedule in Table 1.

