**Fig. 1 Fig1:**
[figure not shown]
Study flow diagram. Assessment will be performed during two visits. Eligible participants will be randomly assigned to either the Control Group (CG) or the Intervention Group (IG). Participants in both groups will receive the same educational program. In addition, participants in the IG will undergo the eight-week behaviour intervention aimed at increasing participation in physical activity. Re-assessment will occur following the completion of the intervention period

**Table 1 Tab1:** SPIRIT schedule of study recruitment, intervention and assessments. Group allocation will occur after a regular medical visit at the Pulmonary Division of the University of Sao Paulo Clinics Hospital; t1 = month 1; t2 = month 2; t3 = month 3

Timepoint	STUDY PERIOD				
	Enrolment	Allocation	Post-allocation		
	*-t* _*1*_	0	*t* _*1*_	*t* _*2*_	*t* _*3*_
Enrolment:					
Eligibility screen	X				
Informed consent	X				
Allocation		X			
Interventions:					
Educational programme		X	X		
Behaviour intervention		X	X	X	
Assessments:					
Anthropometric data, comorbidities, medication, onset of asthma, lung function	X				X
Asthma Clinical Control	X				X
Physical Activity levels	X	X	X	X	X
Health-related quality of life		X			X
Asthma exacerbation		X			X
Anxiety and Depression symptoms		X			X

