### Randomisation and blinding

The randomisation sequence will be computer-generated and implemented by an investigator who is unaware of the sequence and is not involved in recruitment, assessment or treatment. The randomisation sequence will be concealed using opaque envelopes that are sequentially numbered as previously described [28]. Each envelope will correspond to one of the two study groups, and an envelope will be picked by the participant after the baseline assessments. The nature of the interventions will preclude the blinding of the participants and blinding of the physiotherapist who will deliver the education and behaviour intervention. However, the outcome and the statistic assessor will be blinded to group allocation.

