#### Behaviour intervention

Participants in the IG will undergo a behaviour counselling programme, combined with a monitoring-and-feedback tool, which will aim to increase participation in physical activity. The behaviour intervention will be based on the transtheoretical model, which recognizes behaviour change as a dynamic process that moves through stages and that reinforces change via goal-setting, skill-development and self-control [14, 30]. Participants will be requested to attend eight one-on-one face-to-face goal-setting consultations, once a week, with each consultation lasting approximately 40 min. At the beginning of the intervention, a motivational interview will be conducted, in order to identify the physical activity behaviour stage the participant is at, by using a validated questionnaire [31]. Participants will be offered a commercially available activity monitor (wearable device), known as a Fitbit Flex 2 (Fitbit Inc., San Francisco, CA, USA), to wear during the 3 days prior to each consultation. During each weekly consultation, data from the activity monitor will be downloaded and reviewed. An individual action plan, tailored according to each participant’s level of physical activity and behaviour change stage, will be established with realistic goals in order to increase the time spent in physical activity. After 3 weeks of intervention, discussion about sedentary behaviour will be implemented to raise awareness of the risks of prolonged uninterrupted periods of sitting in order to reduce time spent sedentary (i.e. sitting, reclining or lying during waking hours). Participants will be asked to complete a physical activity diary (daily book) and sign a contract with the health professional in order to commit to an action plan.

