### Data analysis

A sample of 46 participants has been estimated as the number needed to provide 80% power in order to detect a between-group difference (favouring the IG) of 0.5 ± 0.7 in the ACQ score (effect size of 0.7) [34]. The final sample size will be set at 55 patients, assuming up to a 20% loss during follow-up, as described previously [8, 29]. The results will be analysed according to the intention-to-treat principle, as recommended by the CONSORT statement [45], using specific software (SigmaStat 3.5, Systat Software Inc.). The distribution of the data for the continuous outcomes will be assessed using the Shapiro Wilk test. Data that are not normally distributed will be transformed, and a repeated measure ANOVA will be used to test the interactions between time and treatment. A Holm-Sidak correction will be applied in order to adjust for multiple comparisons. *P* values < 0.05 will be considered statistically significant.

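### The article claims intention-to-treat, but its two-time-point repeated-measures ANOVA, without an imputation step, uses only participants with a follow-up ACQ: at the planned loss ceiling, up to 11 of 55 contribute nothing

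*Protocol article*

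**What the plan says.** The Data analysis section of the protocol article fixes three things together.

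- The principle: "The results will be analysed according to the intention-to-treat principle".
- The test: "a repeated measure ANOVA will be used to test the interactions between time and treatment".
- The loss allowance: the sample is raised from 46 to 55, "assuming up to a 20% loss during follow-up".

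The ACQ, the primary outcome, has one baseline and one follow-up value. Experimental design says "Both before and following the completion of the intervention period, data will be collected on asthma clinical control", the Fig. 1 legend says "Re-assessment will occur following the completion of the intervention period", and Table 1 marks asthma clinical control at -t1 and t3 only. Under Randomisation and blinding, "an envelope will be picked by the participant after the baseline assessments", so a participant lost afterwards has been randomised and normally has a baseline ACQ but no t3 value.

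The article names no analysis set and gives no rule for a missing t3 ACQ, whether imputation or exclusion.

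**The concern.** Most readers take an intention-to-treat label to mean that everyone randomised is in the analysis. The named model cannot do that alone when the only follow-up value is missing. The published result could then rest on completers under a label that suggests otherwise.

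The matter is more than wording if loss is related to outcome. Both arms attend two classes. The intervention arm has a further commitment: "Participants will be requested to attend eight one-on-one face-to-face goal-setting consultations, once a week". Participants also know their allocation. If those who leave the intervention arm are those who did not benefit, an analysis of completers would overstate the effect of being assigned to the programme. That is plausible, but the article has no figure on it.

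**Working it through.** **1. The plan's own figures.** Required number 46, randomised number 55, loss up to 20% (Data analysis).

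- 46 × 1.20 = 55.2, which reproduces the 55.
- 55 × 0.20 = 11 participants without a t3 ACQ at the ceiling.
- 55 − 11 = 44 with both values.

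That 44 falls short of 46 is a separate sample-size matter and is not needed here.

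**2. What the interaction estimates.** With subject effects, a time effect and a time-by-treatment term on two occasions, the estimate is

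(mean change in the intervention arm) − (mean change in the control arm).

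A participant with a baseline value only has no change score. That single observation is fitted exactly by the participant's own subject effect, so it informs neither the estimate nor the residual variance.

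**3. Degrees of freedom, with 11 of 55 lacking follow-up.**

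- All available rows: 55 + 44 = 99 observations; 55 + 2 = 57 parameters; 99 − 57 = 42 residual df.
- Completers only: 44 × 2 = 88 observations; 44 + 2 = 46 parameters; 88 − 46 = 42 residual df.

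**4. Numerical check.** One simulated trial used these assumed inputs: 27 control and 28 intervention participants, baseline ACQ mean 2.2 and SD 0.7, effect −0.5, and 11 follow-up values removed at random.

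| Analysis | Estimate | SE |
|---|---|---|
| Repeated-measures ANOVA, all rows | −0.4997 | 0.1367 |
| Repeated-measures ANOVA, completers | −0.4997 | 0.1367 |
| Mixed model, all rows | −0.4979 | 0.1338 |
| Mixed model, completers | −0.4997 | 0.1367 |

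The two ANOVA rows are the same, so keeping the baseline-only rows in the file changes nothing. The mixed model does use them, but the gain is small: 0.1338/0.1367 = 0.979, an SE about 2% lower. The simulated mixed model let the baseline means differ by arm; the version with a common baseline mean was not run.

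**5. What could be at stake (illustration, not a forecast).** Assume completers in the intervention arm gain 0.5 over control, a fraction p of that arm is lost with no gain, and loss in the control arm is unrelated to outcome. The effect in all randomised is 0.5 × (1 − p) + 0 × p, while the completers show 0.50.

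| p | Effect in all randomised | Ratio of completer effect to it |
|---|---|---|
| 0 | 0.50 | 1.00 |
| 0.10 | 0.45 | 1.11 |
| 0.20 | 0.40 | 1.25 |

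If those lost gained as much as those who stayed, the effect would be 0.50 at every p and there would be no bias. The 0.40 against 0.50 case is the assumed worst corner of this range.

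**The case against.** The strongest reply is that the article contradicts itself nowhere. It states a principle and a model and is silent on missing values, a matter that a condensed article may leave to the full protocol or analysis plan. Intention-to-treat can mean analysis by allocated arm, and values can be imputed before an ANOVA, after which everyone counts. Raising a sample for loss is routine under any method and does not show who is excluded. Missing sessions is not the same as missing the t3 assessment, which both arms have. And a mixed model or standard imputation would still give about 0.50 in the worst-case illustration, unless observed variables predict who is lost.

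Much of this stands. A reader might infer three stronger things that the documents do not support:

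- That up to a fifth of participants will be dropped by rule. The article says no such thing; the 20% is a planning ceiling, and exclusion follows only if nothing is imputed.
- That loss will be heavier in the intervention arm. The extra consultations make it plausible, but no arm-specific figure is given.
- That the effect will be overstated by 25%. That is arithmetic on a chosen scenario.

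What does not stand is that the whole point can be left to another document. The absence of a missing-data rule alone would be no finding. But the article itself publishes the label, the primary model and the expected loss, and the model as named delivers the label, in its usual sense, only with a step that the article does not mention.

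**Conclusion.** The point holds as a mismatch between the label and the named method, to be resolved by changing one or the other. Carried out as written, with no imputation, the primary test rests on participants who have a t3 ACQ. At the plan's ceiling, 11 of the 55 randomised contribute nothing to it.

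This rests on two ACQ time points, which the article states, and on no prior imputation, on which it is silent. Bias is a possibility whose sign and size cannot be fixed from the document. The gain in precision from keeping baseline-only participants is small, so the case for change rests on having an analysis that matches its label and on examining outcome-related loss openly. The change should be made, but the point does not undermine the design.

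**What to change.** - For the primary outcome, replace the repeated-measures ANOVA with a likelihood-based mixed model that takes baseline and t3 ACQ as outcomes and has a common baseline mean. The constraint is justified because allocation follows the baseline assessments. Alternatively, use ANCOVA on baseline ACQ after multiple imputation from arm, baseline ACQ and other baseline variables. Include all randomised participants in the allocated arm.
- Add one sensitivity analysis, because both methods assume missing at random: shift the missing intervention-arm values towards no benefit and report how the estimate moves. Only this step addresses the scenario in the illustration.
- State that the t3 ACQ is sought from every randomised participant, whether or not sessions are attended.
- If the ANOVA is kept without imputation, describe the analysis as completers by allocated arm.

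Cost: a few sentences of protocol text, a small amount of extra analysis and possibly software other than SigmaStat 3.5. No visits are added to the schedule, but reaching participants who have stopped attending takes some effort, since the ACQ as described includes an FEV1 item as well as symptom questions.

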## Methods/design

### Participants

The study will include adults, aged 18 to 60 years, with moderate or severe persistent asthma [1], clinically stable disease (without hospitalizations, emergency care or medication changes for at least 30 days), who have been undergoing medical treatment for at least 6 months [8]. Patients will be required to report that they are not meeting the current guidelines for sufficient physical activity (i.e. performing < 150 min of moderate to vigorous physical activity per week) [26] and should have uncontrolled asthma according to the asthma control questionnaire (i.e. ACQ score > 1.5) [27]. The exclusion criteria will comprise the presence of any underlying lung condition other than asthma; significant cardiovascular or musculoskeletal disease that may compromise the participant’s capacity to participate in physical activity; active cancer; and uncontrolled hypertension or diabetes. People who are participating in other research studies, those who are unable to understand our questionnaire, as well as pregnant women, smokers or ex-smokers (≥ 10 pack-years), will also be excluded.

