### Outcome measures

#### Primary outcome

##### Asthma clinical control

Asthma clinical control will be measured using the Asthma Control Questionnaire (ACQ). The ACQ, a reliable and validated tool [32, 33] that consists of five questions related to asthma symptoms (daytime and night-time symptoms, activity limitations, dyspnoea and wheezing), one question on rescue medication (the use of short-acting β_2_ agonists) and one question on lung function (forced expiratory volume in 1 s [FEV_1_] before bronchodilation expressed as a percent of the predicted value). The score of the ACQ ranges between 0 and 6. Scores lower than 0.75 are associated with good asthma control, whereas scores greater than 1.5 are indicative of poorly controlled asthma [27]. A change of at least 0.5 points in the ACQ score is regarded as being clinically significant [34].

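### The ACQ comparison is fixed as a time-by-treatment ANOVA, which with one pre and one post value is a change-score t-test: valid, but less precise than adjusting for baseline ACQ

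*Protocol article*

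**What the plan says.** The primary outcome is the ACQ score: "Asthma clinical control will be measured using the Asthma Control Questionnaire (ACQ"). On timing, Experimental design states: "Both before and following the completion of the intervention period, data will be collected on asthma clinical control". Table 1 agrees, marking ACQ once at enrolment and once at t3.

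Data analysis gives one between-group test for continuous outcomes: "a repeated measure ANOVA will be used to test the interactions between time and treatment". It is not labelled primary, but no other is given, and no baseline covariate is named anywhere. The same section adds "A Holm-Sidak correction will be applied in order to adjust for multiple comparisons", without listing the comparisons.

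The planning figures are a "between-group difference (favouring the IG) of 0.5 ± 0.7 in the ACQ score (effect size of 0.7"), and "A sample of 46 participants has been estimated as the number needed to provide 80% power". The text does not say whether 0.7 is the SD of the score or of its change. The significance rule is that P "values < 0.05 will be considered statistically significant", with sidedness unstated.

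Entry is restricted on the primary outcome itself: patients "should have uncontrolled asthma according to the asthma control questionnaire (i.e. ACQ score > 1.5"). Randomisation follows the baseline assessments, and no stratification on ACQ is described.

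**The concern.** With two time points, the interaction contrast is the difference between arms in mean change, and its test is a two-sample t-test on change. That subtracts the whole of baseline from follow-up, which is optimal only if the slope of follow-up on baseline is 1. When the slope is smaller, subtraction adds baseline noise to the outcome.

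Two things follow in a trial of this size. Power is lost that the collected data could supply. And if the arms differ at baseline by chance, the estimate is displaced by (1 − slope) times that difference: if the intervention arm starts with worse ACQ its benefit is overstated, and if it starts better the benefit is understated.

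**Working it through.** **Inputs from the protocol article.** Difference 0.5, SD 0.7, 46 evaluable participants, alpha 0.05, entry ACQ > 1.5.

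**Assumed.** 1:1 allocation (23 per arm), a two-sided test, and r from 0.3 to 0.8.

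**The plan's own figure.** The normal approximation gives a total N of 4 × [0.7 × (1.960 + 0.842)/0.5]² ≈ 61.5, hence 62; the t-based answer is 64. So 46 is not reproduced two-sided. With 23 per arm and an SD of 0.7, power is 66% by the noncentral t (68% by the normal approximation). The 66% is the starting point here; the sample-size mismatch is a separate matter.

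**Variance with equal pre and post SDs (s).**
- Change score: 2s²(1 − r)
- ANCOVA residual: s²(1 − r²)
- Ratio, ANCOVA to change: (1 + r)/2, i.e. 0.65 at r = 0.3, 0.75 at 0.5, 0.90 at 0.8

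Example at r = 0.5 with 0.7 as the SD of change: the effective ANCOVA SD is 0.7 × √0.75 = 0.606, and power is 78%.

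**Variance with baseline truncated at 1.5.** Assume an untruncated ACQ mean of 1.5–2.0 and SD of 0.8–0.9. Let v be the variance of baseline after truncation. The slope stays at r and the residual variance at s²(1 − r²). The change score adds (1 − r)²v, so the ratio is s²(1 − r²) / [s²(1 − r²) + (1 − r)²v].

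Example with mean 1.5, SD 0.8, r = 0.5: baseline is half-normal with SD 0.8 × √(1 − 2/π) = 0.482. The ratio is 0.48 / (0.48 + 0.25 × 0.482²) = 0.89. The effective SD is 0.7 × √0.89 = 0.66, and power is 71%.

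**Power at 23 per arm, difference 0.5, two-sided 0.05 (noncentral t).**

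| r | Planned, 0.7 = SD of change | ANCOVA, equal SDs | ANCOVA, truncated baseline | Planned, 0.7 = SD of score | ANCOVA, 0.7 = SD of score |
|---|---|---|---|---|---|
| 0.3 | 66% | 84% | 74–76% | 52% | 70% |
| 0.4 | 66% | 81% | 72–75% | 58% | 73% |
| 0.5 | 66% | 78% | 71–73% | 66% | 78% |
| 0.6 | 66% | 75% | 70–71% | 75% | 84% |
| 0.7 | 66% | 73% | 69–70% | 86% | 91% |
| 0.8 | 66% | 70% | 68% | 96% | 98% |

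The last two columns are untruncated. The formulas ignore the small cost of estimating the slope. Simulation with a score SD of 0.7 and r = 0.5, untruncated, gave 66.7% for the planned test and 77.0% for ANCOVA.

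**Chance baseline imbalance.** The planned estimate shifts by (1 − r) × imbalance. Under the truncated assumptions the baseline SD is 0.48–0.64, so one standard error is 0.482 × √(2/23) = 0.14 to 0.637 × √(2/23) = 0.19 points. The shift runs from 0.14 × 0.2 ≈ 0.03 (r = 0.8) to 0.19 × 0.7 ≈ 0.13 (r = 0.3).

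**Simulation under no effect** (23 per arm, mean 1.7, SD 0.9, r = 0.5, truncated at 1.5). Type I error was about 5% for both methods, with no average bias. In the tenth of trials with the largest baseline excess in the intervention arm (mean imbalance 0.30), the change-score estimate averaged −0.14 and rejected in 7.7%. ANCOVA averaged about 0 and rejected in 4.9%.

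**The case against.** The strongest reply is that nothing is invalid. Allocation is random and follows baseline, the test holds its error rate, and its estimate is unbiased over repeated trials. That stands in full. It is also right that the gain depends on an unstated correlation and becomes small when r is high: if 0.7 is the SD of the score and r is 0.8, the two analyses have 96% and 98% power.

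A reply that an analysis plan may yet specify ANCOVA carries less weight. The article names its test, so a later plan would have to replace that text, not fill a gap in it.

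Three stronger readings are tempting and are not supported:
- **That selecting on ACQ > 1.5 biases the comparison through regression to the mean.** The entry rule applies to both arms before randomisation, so the expected fall is the same in each and cancels in the interaction. Only a chance baseline difference leaves a residue.
- **That truncating baseline pushes the slope below 1.** Selecting on the predictor leaves the slope unchanged; with equal untruncated SDs it stays at r. Truncation narrows the baseline spread, which makes the gain from ANCOVA smaller.
- **That the plan calls for pre/post tests within each arm.** The Holm-Sidak sentence does not name its comparisons, and the article promises no efficacy claim from within-arm change.

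**Conclusion.** The point holds as one of efficiency and of robustness to chance imbalance, not of validity. If 0.7 is the SD of change, baseline adjustment lifts power from 66% to about 68–76% under the truncated assumptions, or to 70–84% if pre and post SDs are equal. If 0.7 is the SD of the score, untruncated, the range is 52–96% as planned against 70–98% adjusted. The displacement from a one-standard-error imbalance is about 0.03–0.13 points, or 6–26% of the 0.5 target.

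These sizes rest on the assumed r, 1:1 allocation, two-sided testing and, for the truncated case, the assumed ACQ distribution; none of these is in the article. The direction does not depend on where r falls within the range shown. This is a free improvement.

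**What to change.** State the primary analysis as an ANCOVA of follow-up ACQ on group with baseline ACQ as covariate, or an equivalent mixed model with a common baseline mean in the two arms. Report the adjusted between-group difference with its 95% CI, which can then be read against the 0.5-point threshold that the article uses. Apply the same model to the continuous secondary outcomes that are measured at baseline. Fix this before any unblinded outcome data are examined, so that the choice of model cannot depend on the results.

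The cost is a change to the analysis wording and one degree of freedom. No additional visit, measurement or participant is needed.
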